### Outcomes

All measurements for both the experimental- and the control group are performed at baseline after receiving the informed consent (T_0_) and before starting the Hartcoach-programme, and after 6 months (T_1_)^a^. Definitions of primary and secondary outcome measures are presented in Table 1. Targets presented in this table reflect the ideal outcomes. However, in the coaching sessions individualized and feasible targets are defined that may not always fully correspond with those ideal outcomes. For example, a patient may strive for less smoking instead of fully quit smoking.

**Table 1 T1:** **Study outcomes, targets and measurements at T**_**0 **_**and T**_**1**_

**Primary outcomes**	**Target**	**Measurement**
BMI	≤25; or at least 5% reduction of bodyweight	Height: measured without shoes, by nurse Weight: measured without coat and shoes, by nurse
Waist circumference	♀ ≤ 88 cm, ♂ ≤ 102 cm	Measured by nurse with a measuring tape halfway between the lowest rib and the top of the hipbone around the abdomen, under (or without) clothing.
Physical activity	≥ 30 min. 5 times per week	Patient questionnaire: Physical Activity Scale for the Elderly (PASE; [20])
Systolic blood pressure	< 140 mmHg	Measured by nurse with an automatic sphygmomanometer. Patient is seated and both arms are measured. Measurement on the arm with the highest systolic blood pressure is repeated. The mean value of these both measurements is registered
Total cholesterol	≤ 5,0 mmol/l	Laboratory^*^
LDL cholesterol	≤ 2,5 mmol/l	Laboratory
HDL cholesterol	≥ 1,0 mmol/l	Laboratory
Diet	2 ounces of vegetables, 2 pieces of fruit, 20–35% energy intake of fat; < 10% energy intake of saturated fat	Patient questionnaire: Maastricht Voedingsvragenlijst[21]
**Secondary outcomes**		
Blood glucose	fasting glucose < 7 mmol/l	Laboratory
HbA1c (%)	< 53 mmol/mol (< 7%)	Laboratory
Smoking	fully quit	Patient questionnaire: Self report, one question
Self management		Patient questionnaire: Self report, five questions
Medication adherence	Full adherence	Patient questionnaire: Adapted Morisky Scale [22]
Quality of life		Patient questionnaire: MacNew Heart Disease Health-related Quality of Life Questionnaire [23]
Depression Anxiety		Patient questionnaire: Hospital Anxiety and Depression Scale (HADS; [24])

^*^ blood values are analysed by the laboratory in the medical centre the patient is treated, according to local standard practice.

In addition to the outcome measures, also gender, educational status, civil status, work status, the occurrence of life events in the past 12 months, ethnicity, cardiovascular history, treatment history, medication use and co morbidity are registered by the research assistant or nurse at baseline. Data are filled in using an electronic questionnaire.

Through a self developed (paper) patient questionnaire smoking, alcohol consumption, self care strategies in relation to coronary diseases and illness perception are measured. At six months, all measurements are repeated, except measurements of demographic characteristics. In addition, usual care received during the six months is registered through a patient dairy, and patients are asked about their experiences with the Hartcoach-programme.

### Randomisation and blinding

After informed consent has been obtained, each patient is randomly assigned to one of the two groups, regardless the medical centre the patient is treated. After the nurse has logged on to a specific portal, the patient is allocated computerized using a PHP RAND function to “Hartcoach + usual care” (experimental group) or to “usual care” alone (control group). The coordinating research centre informs the patient about the randomisation by a written letter. The measurements are performed by research-assistants or nurses in the treating hospital, who are blinded to allocation.

### Sample size calculation

Sample size calculation was based on one of the primary outcomes that were also used in the study of Vale et al (2003), namely total cholesterol. Based on the values found by Vale et al (2003) for total cholesterol (between groups difference of 0.36 mmol / L (95% confidence interval: 0.20-0.53 mmol / L) 160 patients per group would be needed to find statistical significant results (power of 0.80 and alpha of 0.05)[17]. In this study, a sample of 200 patients per group is chosen, to account for dropout.

### Statistical analysis

Data will be analyzed according to the intention-to-treat principle [25]. All patients, irrespective of completion of the Hartcoach-programme, will be included in the analysis. To determine the effect of the Hartcoach-programme, multilevel analysis will be used because the data have an intrinsic hierarchical nature. Patients are "nested" in hospitals and data are therefore not independent, violating a major assumption of traditional statistical procedures. The model we will use is a multilevel mixed model for repeated measures, a method in which all available data are adequately used: both the paired observations of patients who completed the intervention, as the details of the people who did not complete the Hartcoach-study [26].

Bivariate and multivariate analyses will be used to assess the effects of the intervention (compared to controls) on the individual risk factors cholesterol, body mass index, waist circumference, blood pressure, physical activity, diet, glucose, HbA1c and smoking, as well as on medication adherence, self-management, anxiety, depression and quality of life. The mean change in risk factors between 0 and 6 months is compared between intervention and control group. Age, gender, ethnicity, educational status, civil status, work status, the occurrence of life events in the past 12 months, cardiovascular history, medication use and co morbidity will be included as possible covariates. Data will be analyzed with the statistical packages Stata and MLWIN.

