### Intervention

The Hartcoach-programme consists of a period of 6 months in which the coach contacts the patient every four to six weeks by telephone. The Dutch coaches are nurses who are working at the medical call centre of Achmea in Zwolle. They were trained in the spring of 2009 in Australia and additionally participated in a course on Motivational Interviewing in 2011.

Before starting the first coaching session, the baseline values for risk factors and medication use are established.

In each contact, a continuous quality improvement cycle is followed [17]:

1. Education – part 1. Asking questions to establish patients’ knowledge, attitude and beliefs about their risk factors. Questions are asked about medication, physical activity and dietary intake of saturated fat.

2. Education – part 2. The patient is informed and educated about those aspects for which his/her knowledge is insufficient.

3. Assertiveness training / empowerment. The patient is trained to be assertive in his/her relation with the doctor: to obtain the cholesterol level, to agree upon the target cholesterol level, to alter medication or doses if appropriate etc.

4. Goal setting. Negotiating of a plan of action and setting goals to be achieved by the next coaching session.

5. Reassessment at the next coaching session. Patient adherence to the negotiated plan of action is evaluated.

The coaches register per telephone call the date, topics that were discussed, advices given and agreements made. The patient receives a written letter with the most important advices and appointments summarized. Based on these reports, the researchers are able to verify whether the intervention is performed as intended. In daily practice, the coaching cycle is continued until target levels for risk factors are reached, usually in about 6 months. For the purpose of this study, the coaching cycle is set to 6 months exactly, in order to achieve similar post-treatment periods for all patients.

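### Coaches deliver the programme in one arm only, but neither the model nor the sample size allows for clustering by coach; if outcomes differ between coaches, the planned standard errors are too small

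*Protocol article*

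**What the plan says.** Protocol article, Statistical analysis: the reason for a multilevel model is that patients are nested "in hospitals and data are therefore not independent, violating a major assumption of traditional statistical procedures". The model is a multilevel mixed model for repeated measures. Hospital and the repeated measurements within a patient are the only sources of dependence named, and coach is not in the list of possible covariates.

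Sample size calculation: for a difference of 0.36 mmol/L in total cholesterol, "160 patients per group would be needed to find statistical significant results", with "power of 0.80 and alpha of 0.05". The number is raised to 200 per group, and dropout is the only reason given.

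Intervention: "The Dutch coaches are nurses who are working at the medical call centre", and the coach telephones the patient every four to six weeks for six months. On record keeping, "The coaches register per telephone call the date, topics that were discussed, advices given and agreements made". That list does not mention which coach made the call. The control group receives usual care only and is offered the programme after the six-month measurement.

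Design, and Randomisation and blinding: individual patients in five hospitals are randomised, so both arms occur in each hospital.

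**The concern.** The plan's own argument is that patients who share a unit are not independent and that the analysis must reflect this. It applies the argument to hospitals. Because hospital is crossed with treatment arm, a hospital effect common to both arms is largely removed from the comparison. Patients who share a coach are all in the Hartcoach arm, so a coach effect has no counterpart among controls and stays in the variance of the treatment difference.

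Variation between coaches is plausible. The work consists of questioning, education, assertiveness training and negotiated goals with individualised targets, and it can depend on skill. The Discussion foresees wider implementation after positive results, so the inference is meant to reach beyond the nurses who took part.

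At stake are the width of the confidence intervals, the error rate of the test and the meaning of the stated power.

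**Working it through.** **Inputs from the article.** Difference 0.36 mmol/L; power 0.80; alpha 0.05 (two-sided assumed, since sidedness is not stated); 160 per group before dropout, 200 after; individual randomisation to two equal groups.

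**Assumed, because the article does not give them.** Number of coaches c = 4 to 20; coach ICC = 0.01 to 0.05; equal caseloads; one coach per patient.

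**Step 1: the plan's own figure.** No standard deviation is stated, so 160 cannot be reproduced independently. The SD it implies is

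SD = 0.36 × √(160/2) / (1.960 + 0.842) = 1.149 mmol/L.

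With this SD the standard error without clustering is 1.149 × √(2/160) = 0.1285, and power is 80.0%. This is circular, but it fixes the scale. Also, 160/(1 − 0.20) = 200 exactly: with 20% dropout, nothing is left in the 200 for clustering.

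**Step 2: add coach clustering in the Hartcoach arm only.**

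- Design effect in that arm: DE = 1 + (160/c − 1) × ICC
- True SE = 1.149 × √((1 + DE)/160)
- Ratio k = true SE / 0.1285
- Type I error of the planned test: 2 × Φ(−1.960/k)
- Power of a test that uses the true SE: Φ(0.36/true SE − 1.960)
- Rejection rate of the planned test at 0.36: Φ((0.36 − 1.960 × 0.1285)/true SE)

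Example, c = 6 and ICC 0.02: DE = 1 + (26.67 − 1) × 0.02 = 1.51; SE = 1.149 × √(2.51/160) = 0.144; k = 1.12.

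| Coaches | ICC | DE | SE ratio | Type I error, planned test | Rejection at 0.36, planned test | Power, test that accounts for coach |
|---|---|---|---|---|---|---|
| any | 0 | 1.00 | 1.000 | 5.0% | 80% | 80% |
| 20 | 0.01 | 1.07 | 1.017 | 5.4% | 80% | 79% |
| 10 | 0.01 | 1.15 | 1.037 | 5.9% | 79% | 77% |
| 6 | 0.02 | 1.51 | 1.121 | 8.0% | 77% | 70% |
| 20 | 0.05 | 1.35 | 1.084 | 7.1% | 78% | 73% |
| 10 | 0.05 | 1.75 | 1.173 | 9.5% | 76% | 67% |
| 4 | 0.05 | 2.95 | 1.405 | 16% | 73% | 51% |

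The type I error column refers to a null hypothesis of zero average effect with real differences between coaches. These are normal approximations; with few coaches, small-sample degrees of freedom reduce the power of the corrected test further.

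**Step 3: what lower dropout would do.** With all 200 per arm evaluable, power without clustering is 88%. The test that accounts for coach then has 85% (10 coaches, ICC 0.01), 78% (6, 0.02) or 73% (10, 0.05).

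**Step 4: would more patients help?** The variance is SD² × [(2 − ICC)/n + ICC/c], and the second term does not shrink with n. The variance that gives 80% power is SD²/80. With 5 coaches and ICC 0.05, n = 1.95/(1/80 − 0.05/5) = 780 per arm. With 4 coaches and ICC 0.05, the second term alone is 1/80 of SD², so no n is enough.

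**The case against.** **Unknown inputs.** A reader might infer that coach clustering certainly inflates the variance and that the stated power is certainly overstated. The article does not support that. It gives no ICC and no number of coaches, and it does not say that the coaches are few. Common training, one call centre and a fixed five-step cycle argue for modest variation. ICC 0.05 means a between-coach SD of 1.149 × √0.05 = 0.257 mmol/L, which is 71% of the target effect; no passage supports a spread that large. This objection stands, so the point is conditional.

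**Two different tests.** It is tempting to say that the planned test has both an inflated type I error and power as low as 51%. It cannot. The planned test has the inflated error and rejects 73% to 80% of the time at 0.36. The 79% to 51% belongs to a test with the correct standard error.

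**Which null hypothesis.** If the programme does nothing for any patient, coaches add no variation and the error stays near 5%. The inflation needs a zero average with some coaches doing better than others. This stands as a limit.

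**Net power.** Baseline values in the repeated-measures model, covariates or dropout below 20% may recover power, so net power below 80% is not shown. None of these repairs a standard error that ignores coach.

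**Hospital is a legitimate level, and an article is brief.** The first half is right: blood is analysed in each hospital's own laboratory, and hospital should stay. The second half does not remove the point, because the article states both its hierarchy and its reason for inflating the sample size, and coach is in neither.

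**Conclusion.** The point holds conditionally. The plan names hospital as its only clustering level and makes no sample size allowance for clustering, although coaches deliver the intervention in one arm only. If outcomes vary between coaches, the planned standard errors for the treatment effect are too small, and the 80% power calculated for 160 per group holds only at a coach ICC of 0.

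Over the assumed range, the understatement of the standard error runs from negligible (about 2%, with 20 coaches and ICC 0.01) to serious (about 40%, with 4 coaches and ICC 0.05). The matching range is 5.4% to 16% for the planned test's type I error and 79% to 51% for the power of a test that accounts for coach. All of this rests on the implied SD of 1.149, 160 analysed per arm, equal caseloads and one coach per patient; the last is suggested by the wording of the Intervention section but not stated. It is a cheap improvement worth making, not proof that the trial is underpowered.

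**What to change.** 1. Record the coach identifier for each Hartcoach patient, and for each call if coaches can change. The items listed for the call record do not include it, and without it the correction may become impossible later.
2. In Statistical analysis, specify a partially nested model: a coach random effect in the Hartcoach arm only, controls treated as singletons, hospital kept in the model, and small-sample degrees of freedom. If patients switch coaches, assign the main or first coach by a rule fixed in advance, or use a multiple-membership term.
3. In Sample size calculation, state that 80% power assumes no clustering by coach, and give the power over a stated range of coach numbers and ICCs.

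The cost is one variable and one random term in multilevel software that is already planned. Intervals will be somewhat wider, and with few coaches the coach variance will be estimated imprecisely. No extra patients are needed for this change; with few coaches, adding patients would recover little power in any case.

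### The effect is defined as a difference in mean change, without baseline adjustment or a common baseline mean; read with arm-specific baselines, this gives up precision

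*Protocol article*

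**What the plan says.** The Statistical analysis section fixes three things that bear on this point.

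- The model: "The model we will use is a multilevel mixed model for repeated measures, a method in which all available data are adequately used". Patients are nested in hospitals, and patients who do not complete the study stay in the analysis.
- The contrast: "The mean change in risk factors between 0 and 6 months is compared between intervention and control group". The abstract likewise describes the primary outcome as a change in risk factors.
- The covariates, ten in all and only possible ones: "Age, gender, ethnicity, educational status, civil status, work status, the occurrence of life events in the past 12 months", then "cardiovascular history, medication use and co morbidity will be included as possible covariates". The outcome's own value at T0 is not among them.

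The baseline values will exist. The Outcomes section says: "All measurements for both the experimental- and the control group are performed at baseline after receiving the informed consent", with a repeat at 6 months.

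The section does not say whether the model estimates one baseline mean for both arms or one for each arm.

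**The concern.** When each patient is measured twice, the treatment effect on a continuous outcome can be taken in two main ways from the same data.

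1. Give each arm its own mean at T0 and at T1, and compare the changes. With complete data this is the plain difference in change scores.
2. Use the fact that randomisation makes the true baseline means equal. Either hold them equal in the mixed model, or regress the 6-month value on the baseline value.

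Both estimate the same effect. With equal variances at the two visits, the first subtracts the whole observed baseline difference between the arms, although only a fraction rho of it (the baseline-to-6-month correlation) is expected to persist to 6 months. It therefore has the larger variance whenever rho is below 1.

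A comparison of mean change, with no baseline value among the covariates and no mention of a common baseline, most naturally describes the first way. At stake is the width of the confidence interval for every continuous outcome. The Discussion section itself warns that added effects may be too small to detect where patients also attend intensive rehabilitation.

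**Working it through.** **Inputs from the article.** For total cholesterol, the Sample size calculation section gives a "between groups difference of 0.36 mmol / L (95% confidence interval: 0.20-0.53 mmol / L") and states that "160 patients per group would be needed to find statistical significant results (power of 0.80 and alpha of 0.05"). It then says that "a sample of 200 patients per group is chosen, to account for dropout". It gives no SD, no correlation and no dropout rate.

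**Assumptions.** Equal variance s² at T0 and T1. Baseline-to-6-month correlation rho of 0.3, 0.5, 0.7 or 0.9. All N = 200 per arm measured at T0 and n = 160 at T1, with dropout unrelated to outcome. Hospital effects and the other covariates are left out.

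**The plan's own figure.** 160/(1 − 0.20) = 200, so the last step reproduces with an implied 20% dropout. The 160 cannot be checked without an SD. Solving n = 2·SD²·(1.96 + 0.84)²/difference² backwards (two-sided alpha assumed) gives SD = 0.36 × √80 / 2.80 = 1.149 mmol/L. If the lower confidence limit of 0.20 was used instead, SD = 0.639. Nor does the section say whether the SD is that of a single measurement or of a change.

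**Complete data.** Per-patient variance of the two contrasts:

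- change score: 2s²(1 − rho)
- baseline-adjusted: s²(1 − rho²)
- ratio, adjusted to change: (1 + rho)/2 = 0.65, 0.75, 0.85 and 0.95

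The difference is s²(1 − rho)². This is exactly the variance from carrying chance baseline imbalance into the contrast with weight (1 − rho). Lost precision and uncorrected imbalance are therefore one cost and should not be counted twice.

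**With the dropout that the article allows for.** The mixed model also uses the T0 values of patients lost to follow-up, so it does slightly better than change scores in completers:

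- free baseline means: 2s²[(1 − rho²)/160 + (1 − rho)²/200]
- common baseline mean, or adjusted: 2s²(1 − rho²)/160

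| rho | (1 − rho²)/160 | (1 − rho)²/200 | variance ratio | saving in variance | narrower interval |
|---|---|---|---|---|---|
| 0.3 | 0.005688 | 0.002450 | 0.70 | 30% | 16% |
| 0.5 | 0.004688 | 0.001250 | 0.79 | 21% | 11% |
| 0.7 | 0.003188 | 0.000450 | 0.88 | 12% | 6% |
| 0.9 | 0.001188 | 0.000050 | 0.96 | 4% | 2% |

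The variance ratio is the first term divided by the sum of both. The last column is one minus its square root.

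**Simulation.** In 4,000 simulated trials per setting (200 per arm, each patient missing at T1 with probability 20%, SD 1.149, true effect −0.36), the variance ratio was 0.81 at rho 0.5 and 0.89 at rho 0.7, within about 0.02 of the formula. Mean estimates were −0.363 (free baseline) and −0.364 (adjusted) at rho 0.5, and −0.360 for both at rho 0.7. Neither method is biased.

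**The case against.** The strongest reply is that the plan names a repeated-measures model. The T0 value is then a response, so its absence from a covariate list is expected. If that model holds the baseline means equal, the group effect at T1 is itself the difference in mean change, and the quoted sentence describes the efficient analysis. A condensed article may also leave this detail to a full analysis plan that is not shown. Most of this stands: the article does not rule out the efficient model. What remains is that the article does fix the contrast and does list the covariates, and those two statements fit the less precise model most naturally.

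Four stronger conclusions might be inferred, and the documents do not support them.

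- *The trial will analyse unadjusted change scores and ignore baseline.* The mixed model and the possible covariates say otherwise.
- *The result would be invalid.* Under randomisation the change contrast is unbiased. The cost is efficiency.
- *Simple computerised allocation makes the problem worse.* Blocking would not balance cholesterol or BMI, and stratifying by hospital would remove only differences between hospitals. With about 200 per arm, chance imbalance in a patient-level measurement is almost the same either way.
- *Power would rise by a known amount.* At rho 0.5, power at 160 per group would go from 0.80 to 0.90 if the implied SD of 1.149 were the SD of change. If it were instead the SD of a single measurement, change-score power at 160 would be 0.66 at rho 0.3 and 0.95 at rho 0.7. The article does not say which applies.

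**Conclusion.** The point holds as one of efficiency. As worded, the section most naturally describes a group-by-time contrast with arm-specific baselines, and it does not state the one condition, a common baseline mean, that would make that contrast efficient. Under the arm-specific reading, the baseline-adjusted variance is about 0.70 to 0.96 of the planned one for correlations from 0.3 to 0.9, given equal variances and 160 of 200 per arm followed up. The loss is appreciable for outcomes that track weakly over 6 months and small for those that track closely. The article gives no correlation for any outcome, so no single figure can be assigned. The point concerns continuous outcomes only, so it does not extend to smoking status.

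**What to change.** In the Statistical analysis section, replace the sentence on mean change with a definition of the effect. For each continuous outcome, it is the between-group difference at 6 months, from either:

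- the planned mixed model with one baseline mean common to both arms, so that the group effect enters only at T1; or
- a model of the 6-month value with the same outcome's baseline value as covariate.

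Hospital stays in the model in both cases. Mean change per arm may still be reported descriptively. If the full analysis plan already holds the baseline means equal, saying so is enough.

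The cost is one sentence of model specification, with no new data. It should be settled before the outcome data are compared by arm.
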